## Abstract

**Background:**

Patients with comorbid depression and personality disorders suffer from a heavy disease burden while tailored treatment options are limited, accounting for a high psychological and economic burden. Little is known about the effect of treatment dosage and type of psychotherapy for this specific co-morbid patient population, in terms of treatment-effect and cost-effectiveness. This study aims to compare treatment outcome of 25 versus 50 individual therapy sessions in a year. We expect the 50-session condition to be more effective in treating depression and maintaining the effect. Secondary objectives will be addressed in order to find therapy-specific and non-specific mechanisms of change.

**Methods:**

In a mono-center pragmatic randomized controlled trial with a 2 × 2 factorial design, 200 patients with a depressive disorder and personality disorder(s) will be included. Patients will be recruited from a Dutch mental health care institute for personality disorders. They will be randomized over therapy dosage (25 vs 50 sessions in a year) and type of therapy (schema therapy vs short-term psychodynamic supportive psychotherapy). The primary clinical outcome measure will be depression severity and remission. Changes in personality functioning and quality of life will be investigated as secondary outcomes. A priori postulated effect moderators and mediators will be collected as well. All patients are assessed at baseline and at 1, 2, 3, 6, 9–12 months (end of therapy) and at follow up (6 and 12 months after end of treatment). Alongside the trial, an economic evaluation will be conducted. Costs will be collected from a societal perspective.

**Discussion:**

This trial will be the first to compare two psychotherapy dosages in patients with both depression and personality disorders. Insight in the effect of treatment dosage for this patient group will contribute to both higher treatment effectiveness and lower costs. In addition, this study will contribute to the limited evidence base on treating patients with both depression and personality disorders. Understanding the processes that account for the therapeutic changes could help to gain insight in what works for whom.

**Trial registration:**

This trial has been registered on July 20th 2016, Netherlands Trial Register, part of the Dutch Cochrane Centre (NTR5941).

## Background

Depressive disorders and personality disorders (PD) often co-occur [1–3]. Both depressive disorders and personality disorders are highly invalidating conditions and they represent a tremendous financial burden on society [4–7]. A meta-analysis on the influence of PD on outcome of depression showed that treatment is two times less effective for depressed patients with PD than those without PD [8].This review is based on pretreatment predictor analyses of outcomes in 34 studies with broad samples of depressed patients. Vice versa, research on the impact of a comorbid depressive disorder on recovery of PD is scarce. In an randomized clinical trial (RCT) with mainly cluster-C patients, co-occurring depressions were associated with lower recovery rates at 3 year follow-up (*p* = 0.01). This effect disappeared when controlled for general severity [3], suggesting that not the depressive disorder but high general severity at baseline is a negative predictor for success. In a study on the impact of dysthymic disorder on the outcome in PD patients however, a dysthymic disorder at baseline was related to the persistence of PD diagnoses at 2 years, especially for Borderline PD and Avoidant PD [9].

Despite the urgent need to extend our knowledge of treatment effect in the co-morbid group of patients with both depression and PD, until recently available empirically supported treatments (EST’s) have addressed either depression symptoms or personality pathology. In recent years more integrated therapies such as Schema Therapy (ST) and Short-term Psychodynamic Supportive Psychotherapy (SPSP) have been developed, focusing on depression in relation to inter- and intrapersonal patterns while taking into account etiologic long standing personality vulnerabilities.

Of these, psychodynamic therapies are promising as they are directed at long standing inter- and intrapersonal patterns relating to depression [10]. Evidence for the psychodynamic approach in depression has been demonstrated in a number of meta-analyses [11, 12] and in recent empirical studies [13, 14].

In addition, ST is an integrated psychotherapy originally designed to treat PD and chronic axis-I disorders using techniques from cognitive behavioral therapy, psychoanalytic object relations theory, attachment theory and Gestalt therapy [15]. A study on ST in patients with PD shows a concurrent improvement in depressive symptoms [16] indicating ST might be effective in PD patients with comorbid depression. An adapted form of ST for chronic depression has been described [17] and its efficacy has been demonstrated [18–20].

### Psychotherapy dosage

There are indications that psychotherapy dosage (operationalized as the number of sessions, treatment intensity or treatment duration) is a relevant factor for outcome in both personality disorders and depression. A meta-analysis in Cognitive Behavioral Analysis System of Psychotherapy (CBASP), designed for chronic depression and originally studied for 16 sessions, reports better outcomes when patients received more sessions [21]. For depression, most EST’s consist of 12–20 treatment sessions, but in more complex patients a higher number of sessions is not unusual, varying from 32 sessions in 1 year for patients with depression receiving ST [18] to 60 sessions of psychodynamic treatment within 18 months for patients with chronic depression and at least two failed treatment attempts [22]. For personality disorders, it is widely believed that more sessions are required [23–27] and most evidence based psychotherapies have a duration of at least 1 year. Nevertheless, Kool and colleagues [28] showed that not only depressive symptoms but also personality traits improved after only 16 sessions of SPSP in cluster-C patients. In addition, Bamelis et al. [16] found 50 sessions of ST to be more effective than treatment as usual in treating personality disorders and depression.

The frequency of sessions also appears to moderate effectiveness. A meta-analysis on session frequency in depressed patients found an effect size of d = .45 in favor of having twice weekly sessions versus once a week [29]. The effect of session frequency still needs to be tested directly in a randomized trial and an RCT comparing two dosages of Inter Personal Therapy (IPT) and Cognitive Behavioral Therapy (CBT) in a broad sample of depressed patients is now ongoing [30]. In PD, naturalistic studies focusing on intensity of treatment yield conflicting results. While Kordy and colleagues did not find an advantage of more frequent therapy sessions [26], others reported higher session frequency or treatment intensity to be related to better outcome [25, 31–33].

Taken together, the dosage issue seems to be a relevant factor in depressed patients and might be especially important when personality pathology underlies the (recurrent or chronic) depression. But it is unclear which treatment duration or intensity is needed to achieve enough improvement to prevent relapse.

### Objective

The main objective of the present study is to gather insight in the effect of treatment dosage on therapy outcome in patients meeting criteria of both a depressive disorder and PD, according to the Diagnostic Statistical Manual IV (DSM-IV) or -when available- 5 (DSM-5). We will compare two dosages of psychotherapy; 25 versus 50 sessions within a fixed period of 9 to 12 months in all conditions. SPSP and ST were selected as feasible approaches for this patient group in view of the available evidence for addressing depressive symptoms in the context of personality pathology. The primary hypothesis is that the 50 sessions condition is more effective in treating depression, as shown by a stronger reduction of depression severity and higher remission rates of depression.

Secondary we hypothesize a stronger reduction of susceptibility to depression in the 50 sessions condition by improvement of personality functioning as expressed at DSM-5 level, interpersonal functioning, schemas, schema modes and psychodynamic personality functioning. When personality vulnerabilities can be diminished during treatment, a sustained therapy effect is conceivable leading to less recurrence of depression. Cost-effectiveness will be evaluated at 1 year follow-up.

Additionally, secondary objectives will be addressed in this study in order to find therapy-specific and non-specific mechanisms of change. ST and SPSP have a different perspective on personality pathology: in ST PD are reflected in dysfunctional schemas and schema modes whereas in SPSP dysfunctional patterns in inter- and intrapersonal functioning reflect the personality problems. Although we expect improvement on all these measures in both treatment conditions, this enables us to explore whether the improvement of schemas and schema modes is larger in ST and improvement in inter- and intrapersonal functioning is larger in SPSP. Secondly, ST and SPSP are theoretically characterized by different working mechanisms: the presumed working mechanism of ST is the activation of dominant schemas reflected in schema modes during the sessions. It is explored to what extent this activation during the course of therapy precedes change. In SPSP adequate psychoanalytic support is the presumed working mechanism [34]. By measuring the subscales of the Working Alliance Inventory (WAI-sf) we will explore the aspects of the therapeutic alliance (agreement on goals, collaboration on tasks and therapeutic bond) as a mediator. SPSP can be placed on a variable point on the expressive-supportive continuum and interventions are adjusted to the level of insight the patient is capable of. We will check the hypothesis that the level of insight is not related to outcome. Finally, working alliance is a well-established mediator for change across all therapies [35] especially early measured working alliance [36]. In particular in this group of difficult to treat patients we expect a strong working alliance to be a predictor of positive treatment outcome in all conditions.

To our knowledge this is the first randomized dosage-effect-study for patients with both depression and PD. In addition, despite its high prevalence and clear indications that patients with depression and PD are more difficult to treat, effect-studies on tailored treatment modalities for this specific patient group are scarce.

## Methods/design

### Design of the study

A mono-center pragmatic randomized controlled trial with a 2 × 2 factorial design will be conducted with four parallel groups: 1) SPSP-25; 25 sessions of SPSP (*n* = 50), 2) ST-25; 25 sessions of ST (n = 50), 3) SPSP-50; 50 sessions of SPSP (n=50), 4) ST-50; 50 sessions of ST (n = 50). There is a fixed therapy duration of 9–12 months resulting in the same therapy-duration in all conditions, but different numbers of sessions and different session frequencies: in the 25-conditions once a week sessions during the first 4-6 months (16 sessions) will be followed by fortnightly sessions during the last 4-6 months (9 sessions). The 50-condition starts with a frequency of two sessions a week (32 sessions) followed by weekly sessions (18 sessions). The study follows a 2 × 2 factorial design that allows the comparison of dosage (25 vs 50 session in 1 year) in the combined therapy groups (ST + SPSP) and vice versa. The Medical Ethics Committee of VU University Amsterdam approved the study protocol (registration-number NL55916.029.15). The study is registered at the Netherlands Trial Register, part of the Dutch Cochrane Center (NTR5941).

### Participants

The study is conducted at the NPI, specialist in PD on two locations in Amsterdam (North and East). General criteria for referral are either insufficient results of earlier psychiatric or psychologic treatment or recurrence of depressive symptoms, clinically attributed to PD.

We aim to include 200 patients who meet the following criteria: 1) a DSM-5 depressive disorder (major depressive disorder or persistent depressive disorder) *and* one or more DSM-5 personality disorders, and 2) age 18–65 years. Patients will be excluded in case they: 1) are non-Dutch speakers/readers, 2) have psychotic symptoms, a bipolar disorder or current extreme substance dependence, 3) are in need of immediate and intensive treatment or hospitalization, e.g. acute suicidality according to the intake clinician, 4) are pregnant or unavailable for an uninterrupted period of more than 4 weeks 5) use medication which highly influences mental functioning according to a psychiatrist. No additional psychotherapy can be provided when participating in the trial, as this would exceed the assigned psychotherapy dosage. However, a psychiatrist can be consulted and pharmacotherapy can be provided if indicated. The consultation of psychiatrists and the prescribed pharmacotherapy during the trial will be monitored on the basis of information from the electronic prescription system as presented in Table 1. The Mini International Neuropsychiatric Interview-plus (MINI-plus) section A (Depression) and B (Dysthymia) will be used to diagnose depressive disorders until a version of the MINI-plus is available for DSM-5. The SCID-screener (SCID-PQ / SCID-5-SPQ) followed by the Structured Clinical Interview for DSM-IV personality disorders (SCID-II) or when available DSM-5 (SCID-5-PD) will be used to determine personality disorders.

**Table 1 Tab1:** Monitoring of the pharmacotherapy delivered during the trial

Medication type	Dosage	Start date	End date
Antidepressants	ᅟ		
Benzodiazepinen			
Antipsychotics			
Other medication			

### Sample size

We powered the study to detect a difference of d = .45 between groups for depressive symptoms (BDI-II) [29] given the meta-analysis of session frequency in depressed patients described above, which reported an effect size of 0.45 when treatment sessions were given twice rather than once a week [29].According to this effect size (and given our choices of α = 0.05, two-tailed, power (1-β) = 0.80) 78 patients are needed in both dosage-groups. When 25% dropout is taken into account at least 200 patients will be needed for inclusion. With this sample size differences between SPSP and ST can be detected (with ≥80% certainty) if they differ at least d = .45.

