### Randomization and procedure

An independent research assistant will contact eligible patients within a week after intake and will invite the patient for research assessment. Additional information about the study is provided by email, giving the patient the time to consider participation. During the assessment meeting any doubts or questions about participating in the study can be discussed with the research assistant. The MINI-plus (section A and B) and the BDI-II will be assessed during research assessment and if no structured diagnostic interview has been completed during intake, the SCID-II / SCID-5-PD will be conducted. If the patient is eligible and willing to participate an informed consent is signed. Patients will then be randomized by one of two research department employees in one of four groups (with a 1:1:1:1 allocation) using a computer script performing block randomization (25 vs 50-sessions; ST vs SPSP). Randomization will be pre-stratified according to depression severity (BDI-II < =29 low, BDI-II= > 30 high). Treatment starts as soon as possible (approximately within 0 to 3 months) and patients are assigned to a therapist based on the allocated condition and the therapists availability. Patients will be assigned for the online baseline assessment in the week prior to the start of therapy. During the course of treatment patients will be requested to fill in short online assessments at 1, 2 and 3 months. At 6 months, end of treatment and follow-up extra questionnaires are added. The data collection process is monitored in detail and patients who don’t fill out the questionnaires will be reminded by the research assistant. In addition to the online measurements the SCID-II / SCID-5-PD and MINI-plus (section A and B) will be assessed at treatment termination (9–12 months) and follow-up (21–24 months) by a research assistant who is blind for condition. All data collected from interviews during research assessment at baseline, end of treatment and follow up will be entered and stored on site. Online submitted data forms are converted to the onsite database by the data analyst. All online submitted data will be checked by a research assistant on missing data or specific errors. Independent random data checks will be conducted on entry and encoding errors. All data is entered electronically. As part of the analysis, standard checks on double data entry and range checks on data values will be performed.

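### The 25% dropout allowance does not follow from the plan's own inputs: 78 evaluable patients per dosage group needs 208 included, not 200, a small shortfall that calls for a restated figure

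*Protocol article*

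**What the plan says.** The Sample size section of the protocol article bases the calculation on a standardised difference of 0.45 on the BDI-II between dosage groups, with "α = 0.05, two-tailed" and "power (1-β) = 0.80". From this it concludes that "78 patients are needed in both dosage-groups". The next sentence allows for dropout: "When 25% dropout is taken into account at least 200 patients will be needed for inclusion". The section closes with a claim about therapy type: "With this sample size differences between SPSP and ST can be detected (with ≥80% certainty) if they differ at least d = .45".

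The total of 200 is then used as the planned number. The Participants section says "We aim to include 200 patients who meet the following criteria", and Design of the study splits this into four cells of 50. Patients are randomised "with a 1:1:1:1 allocation", so both the dosage contrast and the therapy contrast compare 100 with 100 before any loss.

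**The concern.** The section names the number of patients needed at analysis and the fraction expected to be lost. Together these fix the number to include, and the number given is smaller. It is worded as a minimum, so rounding does not explain it, and the design adopts exactly 200, so there is no reserve elsewhere.

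This is the power statement for the primary question. If the dosage comparison shows no difference, readers will use it to judge what the trial could have detected. The sentence on SPSP versus ST rests on the same total and the same 1:1 split, so it inherits the mismatch.

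**Working it through.** **Inputs**, all from the protocol article: d = 0.45 (so SD = 1), two-sided α = 0.05, power 0.80, 78 per dosage group, 25% dropout and a total of 200 (Sample size); equal allocation (Randomization and procedure).

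**Step 1. Reproduce the 78.** With the normal approximation,

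n per group = 2(z₀.₉₇₅ + z₀.₈₀)²/d² = 2(1.960 + 0.842)²/0.45² = 77.5, rounded up to 78.

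The plan's figure is confirmed. A t-test calculation gives 78.5, so 79, which is a trivial difference. The requirement is 2 × 78 = 156 evaluable patients.

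**Step 2. Allow for 25% dropout.** If a fraction 0.25 of those included is lost, N × (1 − 0.25) must reach 156:

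N = 156/0.75 = 208, that is 104 per dosage group or 52 per cell.

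The stated 200 is 8 short, or 8/208 = 3.8%. Multiplying instead of dividing gives 156 × 1.25 = 195, and 200 would fit that figure rounded up. The article does not show this step, so it is only a possible explanation.

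**Step 3. What 200 gives at 25% loss.** 200 × 0.75 = 150, or 75 per group, against the 78 stated as needed.

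Power for d = 0.45 in a two-group comparison of completers, normal approximation: Φ(d√(n/2) − 1.960). At 75 per group this is Φ(0.45 × √37.5 − 1.960) = Φ(2.756 − 1.960) = 0.787.

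| Analysed per group | Power, normal | Power, t-test | d at 80% power (normal / t-test) |
|---|---|---|---|
| 75 (200 included, 25% lost) | 78.7% | 78.2% | 0.457 / 0.460 |
| 78 (as stated) | 80.2% | 79.7% | 0.449 / 0.451 |
| 80 (200 included, 20% lost) | 81.2% | 80.8% | 0.443 / 0.446 |
| 100 (no loss) | 88.9% | 88.6% | 0.396 / 0.398 |

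Like for like, going from 78 to 75 per group costs 80.2 − 78.7 = 1.5 points (normal) or 79.7 − 78.2 = 1.5 points (t-test).

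**Step 4. The dropout that 200 does cover.** 1 − 156/200 = 0.22, so 22%.

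**Step 5. The SPSP versus ST sentence.** The therapy contrast also compares 100 with 100, so at 25% loss the first row of the table applies: 78 to 79% at d = 0.45, not at least 80%.

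**The case against.** The strongest reply is that the completers calculation is not the planned analysis. Under Randomization and procedure, stopping treatment early does not end study participation, and those patients are asked to complete all remaining assessments. Under Data analyses, the primary comparison is an intention-to-treat linear mixed model, and Table 2 schedules the BDI-II repeatedly before, during and after therapy, so patients with incomplete series still contribute. The article does not say what the 25% refers to. If it is treatment dropout with assessments retained, up to 200 patients could be analysed, which gives about 89% power on the simple test.

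This stands as an argument about the consequence. A reader might infer from Step 3 that the trial fails to deliver its 80% power, but the document does not support that. Power under the planned four-level model cannot be worked out from the article, which gives neither the correlation between repeated BDI-II scores nor the clustering by therapist. The first would tend to raise power and the second to lower it. For example, if the comparison of 150 completers were adjusted for baseline BDI-II, a baseline-to-outcome correlation of 0.1, 0.2, 0.3 or 0.5 would give about 79%, 80%, 82% or 89% (t-test), and about 0.22 is enough to restore 80%. These correlations are assumptions, not figures from the article.

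The reply does not rescue the inflation step. The Sample size section invokes neither repeated measures nor retained dropouts. It gives a two-group calculation followed by a dropout allowance, and 200 does not follow from 156 and 25% under either meaning of dropout.

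It is also fair to say that the gap is small and that the therapy contrast is secondary, with its limited power already acknowledged in the Discussion. Both points bear on the weight of the finding, not on its correctness.

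**Conclusion.** The total is wrong on its own assumptions: 78 evaluable per dosage group with 25% loss needs 208 included, and the article states 200 as sufficient. The size of the error is 8 patients. In a simple comparison of completers it means about 78 to 79% power at d = 0.45, or 80% power at d = 0.46. This rests on the article's own effect size, α and target power, and on reading the 25% as patients missing from the analysis.

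It is a small arithmetic inconsistency in the primary power statement that should be corrected. It is not evidence that the trial is materially underpowered.

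**What to change.** Keep 200 and correct the sentence in one of two ways:

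- *200 patients will be randomised; with 25% loss to assessment, 150 will be analysed, giving about 78% power for d = 0.45 (80% for d = 0.46).*
- *200 patients will be randomised, which allows for 22% loss to assessment while retaining 78 per dosage group.*

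In either case, say whether the percentage means stopping treatment or loss to assessment. Align the SPSP versus ST sentence with the version chosen: under the first, replace the claim of at least 80% at d = 0.45 with about 78%, or move the difference to 0.46, and bring the matching d = 0.45 limit in the Discussion into line.

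The cost is a few reworded sentences. Recruitment, allocation, outcomes and analysis stay as they are. The first option states slightly lower power; the second rests on expecting fewer losses, so it needs a reason for 22%.

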#### Therapists

All therapists have an academic degree in Psychology or Psychiatry and are health care psychologists, psychotherapists, clinical psychologists or psychiatrists. All participating schema therapists are registered schema therapists in the Netherlands or schema therapists in training. When not yet registered the therapist has at least 6 months experience in ST and receives additional supervision. A 1 day training in ST for depression was given to all therapists in the ST condition by a registered supervisor in ST. The SPSP therapists are registered as SPSP therapists or in training. When not yet registered the therapist has at least 6 months experience in SPSP and receives additional supervision. All registered therapists in de ST or SPSP condition can consult each other in biweekly consultation meetings. All sessions are audio-taped for both supervision- and adherence-purposes.

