### Data analyses

#### Clinical outcome: depression

Data-analysis will include an intention-to-treat analysis. Baseline characteristics and antidepressants used during treatment will be examined in the two dosage conditions (25 and 50 sessions) and potential confounding factors will be added as covariates in the analyses.

The primary outcome measure is depression severity (BDI-II). Relative effectiveness of the two dosage conditions (25- vs 50-sessions) will be analyzed using linear mixed models, with the underlying distributional model based on the distribution of the dependent variable and the residuals (e.g. normal, gamma, negative binomial). With this model missing values can be dealt with effectively. This analysis will be conducted according to a four-level structure (patient, therapist, location and time). The growth curve on depression severity over time can be shown with this model. The proportion of patients that achieve reliable and clinically significant improvement at termination and follow-up will be calculated on the outcome measure (BDI-II) for both dosage conditions, and secondary for both therapy-conditions (ST/SPSP). These calculations will be based on the reliable change index [69]. Comparison between the dosage conditions (and secondary between the therapy-conditions) will be analyzed with generalized estimating equations (GEE). In addition, remission rates will be measured and compared for the dosage conditions (and secondary for the therapy-conditions) at termination and follow-up (MINI-plus, section A and B) using GEE. In exploratory analyses, the interaction of treatment condition and dosage condition will be analyzed for all outcome measures.

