Fourthly, categorical DSM diagnoses were used to measure the inclusion criteria for both depression and PD. Thus nearly legitimate patients were excluded which, in view of the dimensional distribution in the real world of both severity personality pathology and of depressive symptoms, limits the generalization of the study.

Also, the dosage conditions of 25 or 50 sessions were chosen arbitrary and although these dosages can be considered as adequate for treating depression, the dosage is considered to be relatively low for treating PD. If both 25 and 50 sessions would not be sufficient to treat depression in this co-morbid patient group, it could be falsely interpreted that, without clear differences between the groups, the less intensive and less expensive 25 sessions condition would be preferred. Instead, effect sizes must be taken into account and additional research might be necessary to investigate whether higher dosages will lead to better outcomes.

The current study cannot distinguish between session frequency and total amount of sessions because the therapy duration was set to 1 year in all conditions. Thus, in case of significant differences in favor of the 50 sessions, follow-up studies are needed to disentangle the contribution of the number of sessions from the frequency effects.

A last limitation of the study is the fact that it is not powered to detect a clinically relevant difference between SPSP and ST if this would be smaller than d = .45. Even if the study would be powered to be able to detect a difference smaller than d = 0.45, we would not expect a difference between SPSP and ST. However, the study sample is not large enough and therefore underpowered to demonstrate equivalence between both theoretical treatment orientations.

This study aims to contribute to the evidence on psychotherapy for patients with co-occurring depression and personality disorders. Furthermore, this is the first study to compare two psychotherapy-dosages in this comorbid patient group. This study can help to get insight in how frequent and how much psychotherapy is needed to treat these complex patients. And finally, we hope this study will help to understand some of the processes that account for therapeutic changes.

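### The ≥80% power stated for SPSP versus ST at d = .45 assumes independent patients, although therapists appear to be nested in therapy type, so the unqualified figure is unsupported

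*Protocol article*

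**What the plan says.** The Sample size section starts from one effect size: "We powered the study to detect a difference of d = .45 between groups for depressive symptoms (BDI-II". It continues "given our choices of α = 0.05, two-tailed, power (1-β) = 0.80" and concludes that "78 patients are needed in both dosage-groups". Allowing for 25% dropout, it arrives at 200 inclusions, and then extends the result to the other factor: "With this sample size differences between SPSP and ST can be detected (with ≥80% certainty) if they differ at least d = .45". It mentions no therapist ICC, design effect or number of therapists.

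Other sections bear on whether patients are independent for that factor:

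- Randomization and procedure: "patients are assigned to a therapist based on the allocated condition and the therapists availability".
- Therapists: ST and SPSP therapists are described separately, each with their own registration and experience requirement. For ST, "A 1 day training in ST for depression was given to all therapists in the ST condition".
- Level of discourse in SPSP, and Dominant schema mode: each process rating is made by the therapists of that one therapy.
- Clinical outcome: depression: "This analysis will be conducted according to a four-level structure (patient, therapist, location and time".

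The limitations in the Discussion return to the comparison and say that "it is not powered to detect a clinically relevant difference between SPSP and ST if this would be smaller than d = .45".

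**The concern.** If each therapist delivers only one of the two therapies, therapists are nested in the therapy factor. Patients of the same therapist tend to have similar outcomes, and that shared component does not cancel when SPSP is compared with ST. The variance of the difference then grows by the design effect 1 + (m − 1) × ICC, where m is the number of analysed patients per therapist. The analysis plan recognises this level but the power statement does not, so the two rest on different assumptions.

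What is at stake is how a null SPSP-ST result is read. The Discussion says that no difference is expected, so a null is the likely outcome. Readers would take it as coming from a comparison with at least 80% power at d = .45.

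**Working it through.** **Inputs from the protocol.** d = 0.45 (SD = 1); two-sided α = 0.05; power 0.80; 78 per group; 25% dropout; 200 included with 1:1:1:1 allocation, hence 100 per therapy.

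**Assumed inputs (not in the protocol).** Therapist ICC 0.02 to 0.10; 5 to 10 analysed patients per therapist.

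**1. Reproduce the plan's figure.** n per group = 2 × ((1.960 + 0.842)/0.45)² = 77.5, rounded up to 78. This is the two-sample formula for independent patients, and it matches.

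**2. Power at the planned dropout, no clustering.** 200 × 0.75 = 150, or 75 per therapy, not 78. Power = Φ(0.45 × √(75/2) − 1.96) = Φ(0.796) = 78.7%. At 78 per group it is 80.2%. The break-even design effect is 75/77.5 = 0.97, already below 1, so there is no reserve and any positive ICC lowers power further.

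**3. Add therapist clustering.** DE = 1 + (m − 1) × ICC; n_eff = 75/DE; power = Φ(0.45 × √(n_eff/2) − 1.96); detectable d = 2.80 × √(2 × DE/75).

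| m | ICC | DE | n_eff | Power | Detectable d at 80% |
|---|---|---|---|---|---|
| any | 0 | 1.00 | 75.0 | 78.7% | 0.46 |
| 5 | 0.02 | 1.08 | 69.4 | 75.5% | 0.48 |
| 8 | 0.05 | 1.35 | 55.6 | 66.0% | 0.53 |
| 10 | 0.10 | 1.90 | 39.5 | 51.6% | 0.63 |

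The first row is the right baseline: in the mildest scenario clustering costs about 3 points, not the full distance from 80%. These are normal approximations. Testing against the between-therapist degrees of freedom lowers them: with 10 therapists per therapy and ICC 0.05, from 66.8% to 62.0%.

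**4. What could restore 80%.** Hold the number of therapists fixed.

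- *All 100 per therapy analysed.* The break-even design effect rises to 100/77.5 = 1.29. In the mild scenario, 75/5 = 15 therapists now see 6.7 patients each; DE = 1 + 5.67 × 0.02 = 1.11, n_eff = 89.8 and power is 85%.
- *Baseline adjustment, assumed correlation 0.6, therapist variance unreduced.* In the middle scenario there are 75/8 = 9.4 therapists, and the within-therapist variance is 0.95 × (1 − 0.36) = 0.608. At 75 per therapy, SE = √(2 × (0.05/9.375 + 0.608/75)) = 0.164 and power is 78%. At 100, SE = 0.151 and power is 85%.
- *Extreme scenario (m = 10, ICC 0.10).* With both gains together, 75/10 = 7.5 therapists and within-therapist variance 0.90 × 0.64 = 0.576 give SE = √(2 × (0.10/7.5 + 0.576/100)) = 0.195. Power is 63%, still well short.

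**The case against.** The best reply is that the shortfall depends on assumptions. Neither the ICC nor the caseload is given. Patients who stop treatment are asked to stay in all remaining assessments, the analysis is by intention to treat with a mixed model that uses partial data, and the BDI-II is measured at the start of therapy and at seven later points. A small ICC with nearly complete data, or a gain from baseline or repeated measurements, could bring power back to 80%. This stands. A reader might infer that the design cannot reach the stated power; the documents do not support that. What remains is that the Sample size section claims none of these gains and plans on losing 25%.

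A second reply is that the Discussion already guards against over-reading. It says the study's scope does not permit a full check of outcome differences between the therapies, places such differences at an exploratory level, and calls the sample too small to demonstrate equivalence. Its sentence on d = .45 says only that smaller differences are out of reach, which stays true under clustering. A reader might take that sentence as a second error; it is not. These cautions reduce the risk of misreading but do not correct the affirmative claim under Sample size.

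Third, no passage says outright that no therapist delivers both therapies. Separate pools are the natural reading of four sections, but still an inference.

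Finally, a reader might extend the point to the primary dosage comparison. If therapists treat patients in both dosages, which the article does not state, a shared therapist effect largely cancels there. The documents give no ground for saying that comparison is underpowered through clustering.

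**Conclusion.** The point holds in limited form. The ≥80% statement for SPSP versus ST is an independent-patients result applied to a factor in which therapists appear to be nested, in a plan whose own model has a therapist level. An unadjusted comparison at the planned dropout starts at 78.7% and falls to roughly 76%, 66% or 52% across the assumed scenarios. The small gap below 80% before clustering comes from having 75 rather than 78 per group, not from therapists. The exact loss cannot be fixed from the documents, so the claim is unsupported rather than false in every case. It concerns a secondary comparison and one sentence. The planned BDI-II model already handles therapist clustering in the analysis itself.

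**What to change.** In the Sample size section:

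- withdraw the unqualified ≥80% statement for SPSP versus ST, or restate it as the difference detectable at 80% power under a stated therapist ICC, number of therapists per therapy and dropout, naming any gain from baseline adjustment that is relied on;
- say that the 80% planning figure is for the dosage comparison;
- call SPSP versus ST exploratory, in line with the Discussion's second limitation.

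The Discussion's closing limitation needs no correction, only a matching mention of therapist clustering.

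The cost is wording, plus a less favourable stated figure for the therapy comparison. The number of inclusions, the randomisation and the way patients are assigned to therapists all stay as they are.
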